#### Criteria for withdrawal/discontinuation of participants

A participant will be excluded from the study when one of these conditions occurs:withdrawal of the consent at any time of the study.evidence of serious adverse events or accidents incompatible with study continuation.

Furthermore, a subject may be excluded by the study cohort, following autonomous decision of the responsible PI, for any reason or consideration made in the interest of the subject itself or of the classroom.

### Study intervention

#### Identity of investigational products

##### Experimental intervention

The LM is a screening strategy based on molecular analysis for SARS-CoV-2 of pooled saliva samples taken from a group of individuals, in our case a school class including the teacher present in the class at that time. If the pooled sample is positive, then each class students is tested individually and all negative tested students/teachers are permitted to return to school. If the positive is identified, this subject will stay home according to the directions of the health authorities.

The procedure adopts standard material (PCR, swabs, plastic tubes for collection of swabs).

The pooled sample is treated as follows: all swabs from one class are collected in a single Falcon tube. As the Falcon tube enters the lab, 3 ml of PBS will be added to it. After mixing, a portion of the sample will be used for testing. Testing will be performed using standard SARS-CoV-2 PCR diagnostic approaches available in each laboratory.

The samples are collected at the first school hour in the morning. The results of the molecular analysis are provided in the same day. In case of a positive pool, individual saliva re-testing of each class member is performed the day after to identify the positive individuals.

The remaining sample of each positive individual will be stored for long term conservation to further analyse variants by punctual mutation PCR test or by sequencing.

##### Control intervention

The control arm will undergo conventional surveillance based on symptoms prompting testing and contact tracing according to SoC, to identify SARS-CoV-2 positive students, under the supervision of dedicated personnel (local health authorities personnel and/or school personnel). The local PIs and staff will be available to provide support for any questions.

#### Administration of experimental and control interventions

##### Experimental intervention

The children in the experimental group will undergo regular screening for the whole study periods using the LM. This consists of PCR pooled saliva tests as previously described. The main specificity of the approach is that each class is considered as a unit of testing and therefore tested in a single PCR. The teacher present in the class at the time of the test and the school personnel “adopted” by the class will participate in the pool test together with the class. Each pool will include the students, the teacher at the time of sampling and the auxiliary school staff associated to each class.

We will propose the pooled saliva test to each class participating in the study twice a week.

Specifically, each involved person will suck on a swab for 30 s to collect saliva. All swabs from each class will be collected in a single Falcon tube. The tubes of all the participating classes are stored at a safe place in the school and then collected and transported to the lab.

If a class (pool) tests positive, results will be reported to the schools and parents later that day and individuals whose sample were within the positive pool will be re-tested individually the next morning.

The results of the individual tests are provided within the same day or exceptionally the day after. The positive results are transmitted to the relevant health authorities and have the related legal value (involved laboratories are certified, approved laboratories).

The positive subjects and the whole class/school will follow the containment measures foreseen by the national and regional regulations applicable in each country at each moment.

Householders of a positive child will be tested as soon as the child is known positive (day 0), at day 5 and at day 15. The affected householders collect their single swabs at the agreed time points and store them to be analysed after quarantine (retrospectively). This will allow us to determine the transmission route in each family as well as secondary attack rate.

The usual surveillance based on symptoms indicating testing and contact tracing activity will continue according to SoC in the interventional arm too.

Remnants of the samples can be used for re-analysis for other pathogens. This will only be performed after the study group decides to perform such additional analysis. This will be performed retrospectively and anonymously.

##### Control intervention

The classes in the control group, including the assigned teachers and school personnel, will follow SoC countries measures regarding surveillance based on symptoms and contact tracing. The usual surveillance will be conducted by the personnel devoted to it in SoC situation. Study personnel from the involved PIs will be available to support.

### Study assessments

#### Assessments of outcomes

##### Assessment of primary outcome

The frequency of clusters in classrooms will be evaluated. We will compare classrooms where pooled saliva tests (LM) are performed in association with standard contact-tracing protocols, with classrooms in which only standard contact-tracing protocols are applied. The transmission/prevalence of SARS-CoV-2 in schools will be also evaluated, by assessing the proportion of students/staff with positive SARS-CoV-2 test identified by pooled saliva tests (LM).

##### Assessment of secondary outcomes

Comparing SoC with LM, the size of clusters and attack rates in classrooms will be evaluated.

The collected samples will be analysed via each available method for variants detection (for instance: differential PCR /real time PCR/ whole genome sequencing).

The effectiveness of different preventive measures adopted in different schools will be compared. Different types of protocols regarding contact tracing will also be compared.

Secondary transmission attack rate in households will be assessed for positive cases detected by pooled LM. The same assessment will be applied to the study of the SARS-CoV-2 spread dynamics in schools.

Simultaneously with the evaluation of the efficacy of LM, a psychological evaluation of the status of children during the COVID-19 pandemic will be performed (negative and positive feelings during confinement, worries and expectations about school resumption). Data will also be collected in order to study the correlation between environmental or/and temperamental factors and the stress levels reported by the children. For this goal, self-reported quality of life questionnaires will be implemented.

Mobility information and non-pharmaceutical interventions that were enacted in the school's area will be collected and evaluated as potential effect modifiers. This will be done using data collected in public databases, as well as data curated by the local PIs.

##### Assessment of safety outcomes

All safety concerns regarding the usage of the LM will be explained to the kids and their tutors, and every question will be answered at the beginning of the study.

During the intervention, any safety concern of this procedure will be collected via the school director and workers. All situations reported will be taken into consideration regarding that participant’s continuation or premature stop from the study.

#### Procedures at each visit

The Lolli will be performed two days a week, the “Lolli days”. The procedure can be managed autonomously by the schools or with support by an external person from the research centre.

Each Lolli day, the students who participate in the trial are given a swab at the entrance in class. They suck the swab for 30 s and then they all enter their swabs into the same large tube for the class. The teacher and the non-teaching personnel do the same.

The teacher puts a label with the class ID and barcode on the tube and enters into the eCRF the information of questionnaire T1 (date, class identifier, n. of absent pupils, n. of pupils who refused to carry out the test).

The responsible person for each school collects the tubes and puts them into a plastic bag.

The contracted courier authorised to biological samples transportation will then arrive at agreed time and will bring the plastic bag containing all the tubes to the laboratory. Tubes will be sent to the study laboratory in the morning. Results will be returned to the monitor in the same day.

If the pool is positive, the monitor will contact the school and the Public Health authorities in the same day and request the positive class participants to return to school the day after to collect the Lolli test for the individual testing. While waiting for the individual results, the tested participants will return back home or go to school according to the national regulation in force.

The individual results will then be communicated to the relevant public health authorities who will conduct the epidemiological investigation supported by the study questionnaire and will assign the containment measures according to the regulation in force.

The procedures set in place to accomplish the objectives of this project will be monitored during the entirety of the study by the PIs of the centre that enrolled the school.

### Statistical methods

#### Hypothesis

The main hypothesis is that the LM can reduce the frequency of clusters (i.e. two or more cases in a class within a scholar week).

The main endpoint is the frequency of cluster per class in a scholar week.

Secondary endpoints are cluster size and duration of consecutive/serial infections in the same class.

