#### Determination of sample size

Clusters are defined as epidemiologic links between an index patient and one or more persons who likely acquired SARS-CoV-2 infection in class (i.e., class-associated cases). Given the average infection rates in contacts of about 4% per class [31], a sample size of 440 classes (220 per arm) achieves 80% power to detect a difference between the group proportions of 3.5%. The proportion in arm with LM is assumed to be 4% under the null hypothesis and 0.05% under the alternative hypothesis. The test statistic used is the one-sided Z test with pooled variance with a 5% significance level.

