##### Primary analysis (LM evaluation trial)

The number of clusters per class per week will be compared between the two arms: LM + SoC arm vs SoC only. Absolute and relative frequencies of clusters will be reported by arms and compared at univariate analysis with Chi Square or Fisher exact test, as appropriate. Univariate analysis will be performed and the p-values for statistical tests of associations of categorical and continuous variables with the two treatment arms will be reported (Chi square/Fisher exact test and T-test/Wilcoxon sum rank test for categorical and continuous variables, respectively). We will also investigate the psychological impact of Lolli tests and preventive measures to reduce the risk of infections; we will compare the frequency of infections according to socio-economic status, regions, teacher vs student, educational level, also taking into account vaccination rates within each class.

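### The primary-endpoint cluster is defined in two incompatible ways, so the same data can give two primary results and the sample size describes a different event from the one analysed

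*Protocol article*

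**What the plan says.** All of this is in the protocol article.

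- **Hypothesis.** The trial is to "reduce the frequency of clusters (i.e. two or more cases in a class within a scholar week". The endpoint follows: "The main endpoint is the frequency of cluster per class in a scholar week". This is a count inside a time window, with no link required.
- **Determination of sample size.** The rule here is different: "Clusters are defined as epidemiologic links between an index patient and one or more persons who likely acquired SARS-CoV-2 infection in class". This is a transmission link, with no time window.
- **Same section, inputs.** The rate is introduced by "Given the average infection rates in contacts of about 4% per class". The result is that "a sample size of 440 classes (220 per arm) achieves 80% power to detect a difference between the group proportions of 3.5" percentage points. The rates are given as "The proportion in arm with LM is assumed to be 4% under the null hypothesis and 0.05% under the alternative hypothesis", and the test as "The test statistic used is the one-sided Z test with pooled variance with a 5% significance level".
- **Primary analysis (LM evaluation trial).** The comparison is put this way: "The number of clusters per class per week will be compared between the two arms: LM + SoC arm vs SoC only". Whether a link is needed is not stated.
- **Primary outcomes** and **Assessment of primary outcome** name cluster frequency without defining a cluster.
- Verifying transmission within school is a secondary objective, and the duration of serial infections is a secondary endpoint. Neither changes how the primary endpoint is counted.

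**The concern.** A primary endpoint needs one counting rule. Here two are stated as definitions, one attached to the hypothesis and one to the sample size, and they disagree in both directions. The primary result then has no single meaning, and the rule could be settled after the data are seen.

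Each feature of the weekly count also has a cost. Without a link requirement, independent infections from outside school count as clusters. School screening can do little about coincidences of that kind, so they dilute the contrast between arms. With a fixed week boundary, a true chain can be cut in two and missed, and a long outbreak can count in several weeks.

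**Working it through.** **1. The two rules applied to the same events**

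| Event in one class | Weekly count (Hypothesis) | Link rule (Determination of sample size) |
|---|---|---|
| Two unrelated community infections, same week | cluster | no cluster |
| Index case found Friday, linked classmate found next Monday | no cluster | cluster |
| One chain with two or more new cases in each of three weeks | three class-weeks with a cluster | one linked chain |

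The first two rows are enough to show that neither rule is a special case of the other. The second row holds whether the school week is read as Monday-Friday or Monday-Sunday.

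**2. The plan's own sample size**

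One-sided pooled Z test, alpha 0.05, power 80%, 4% against 0.5% (4% less 3.5 points), mean proportion 0.0225:

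n = [1.645·√(2·0.0225·0.9775) + 0.842·√(0.04·0.96 + 0.005·0.995)]² / 0.035² ≈ 221 per arm.

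Power at 220 per arm is 79.8%, so the stated 440 classes are reproduced. With the printed 0.05% instead of 0.5%, n is 157 per arm and power at 220 is 90.5%. That mismatch is a separate matter.

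The calculation uses one proportion per class, and its 4% is an infection rate among contacts. It is therefore not a rate of two or more cases per class-week, which is the event named as the endpoint.

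**3. Coincidence under the weekly count**

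Class size is 8800/440 = 20 (General study design). The weekly risk q of an independent infection per person is an **assumption**; the article says only that incidence will change. With no in-class transmission:

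P(two or more) = 1 − (1−q)^20 − 20q(1−q)^19

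For q = 1%: 1 − 0.8179 − 0.1652 = 0.0169.

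| q per week | 0.1% | 0.25% | 0.5% | 1% | 1.5% | 2% |
|---|---|---|---|---|---|---|
| Class-weeks with two or more cases | 0.02% | 0.12% | 0.45% | 1.7% | 3.6% | 6.0% |

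The background section reports positivity of 0.05% to 2.61% in an earlier roll-out but does not say whether this is per pool or per person. It cannot fix q.

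**4. The week boundary**

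**Assumptions:** first detection even over Monday-Friday; second linked case found exactly g days later. For g = 3 the pairs are Mon–Thu, Tue–Fri, Wed–Sat, Thu–Sun and Fri–Mon.

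- Monday-Friday week: two of five pairs stay together, so 60% are split.
- Monday-Sunday week: four of five stay together, so 20% are split.

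| Gap g (days) | 1 | 2 | 3 | 4 | 5 |
|---|---|---|---|---|---|
| Split, Monday-Friday week | 20% | 40% | 60% | 80% | 100% |
| Split, Monday-Sunday week | 0% | 0% | 20% | 40% | 60% |

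**The case against.** The best defence is that the weekly count is the operational rule and the linked wording only describes the idea behind it. The weekly unit appears with the hypothesis, the endpoint and the primary analysis, while the linked wording appears only under sample size. Making in-school transmission a separate secondary objective also fits a primary count that needs no link. This makes the weekly count the likelier intention. It does not remove the conflict, because the sample-size section states its rule as the definition of a cluster and neither section refers to the other. Nor is this a detail left to an analysis plan: the article gives two answers, and a later document could follow only one.

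A class-week unit is also a legitimate choice, with serial infections and time to first cluster analysed elsewhere. That is fair, but it does not say which cases make up a cluster.

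Several stronger readings are tempting and do not hold:

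- **Coincidence alone exceeds the planned rate in the screening arm.** The chance probability reaches 0.5% at q = 0.53%. But the 0.5% comes from a one-proportion-per-class calculation based on a contact infection rate, so it is not a class-week comparator. For the same reason, adding the chance background to 4% and 0.5%, which would give power of 73% (q = 0.5%) or 59% (q = 1%), is not a supported estimate of lost power.
- **Most linked pairs are lost.** The 60% needs a fixed 3-day gap and a Monday-Friday week. Even spread of detection also fits poorly with an arm tested on two set days a week.
- **The boundary biases the comparison between arms.** Retesting the whole class the day after a positive pool plausibly bunches detections in the screening arm. But contact tracing in the control arm can also find classmates together, and standard surveillance continues in both arms. The documents give nothing from which to size the difference.

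**Conclusion.** The contradiction stands and sits on the primary endpoint. It rests on the text alone: the two rules classify the same events differently, the primary analysis does not choose between them, and the sample size is justified for an event other than the weekly one to be compared.

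The sizes are illustrations. Chance clusters in about 0.02% to 6% of class-weeks assume independent infections, a class of 20 and a weekly risk of 0.1% to 2%. A split of 20% to 60% of linked pairs assumes a 3-day gap and even weekday detection, with the range set by how the school week is read. A reader might infer that the choice of definition will decide the trial, or that it favours one arm. The documents support neither claim, only that the result can differ and that chance clusters dilute an effect.

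**What to change.** Reconcile Hypothesis, Determination of sample size and Primary analysis to one cluster definition, fixed before the outcome data are examined and based on information gathered equally in both arms. One workable form is two or more cases in the same class with first positive samples within 7 days of each other, whatever the week boundary, with each chain counted once. Then restate the sample-size assumption as a rate of that event, in the unit that is analysed. Report the linked definition and the school-week count as sensitivity analyses.

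Do not remove cases with a documented household source from the primary count. Household testing is described only for cases detected in the screening arm (Study population; Administration of experimental and control interventions; Assessment of secondary outcomes). Such an exclusion would therefore fall mainly on that arm and favour it.

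The cost is modest: wording, some analysis work, and a sample-size justification that may look less favourable once the rate matches the event. A common definition does not cancel the difference in how intensively the arms are tested, and a window without a link requirement still admits some chance pairs. The linked sensitivity analysis is there for the latter.

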#### Determination of sample size

Clusters are defined as epidemiologic links between an index patient and one or more persons who likely acquired SARS-CoV-2 infection in class (i.e., class-associated cases). Given the average infection rates in contacts of about 4% per class [31], a sample size of 440 classes (220 per arm) achieves 80% power to detect a difference between the group proportions of 3.5%. The proportion in arm with LM is assumed to be 4% under the null hypothesis and 0.05% under the alternative hypothesis. The test statistic used is the one-sided Z test with pooled variance with a 5% significance level.

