### Study design

#### General study design (Fig. 1)

**Fig. 1 Fig1:**
[figure not shown]
Study flowchart. The flowchart summarize the general study where is divided in two sub studies, (i) interventional study which contains a Lolli arm and a control arm; and (ii) observational study. A detailed description have been written in the main text. We want to acknowledge Pez Beta Design for the elaboration of the figure

A multicenter cluster randomised interventional study will be set-up to evaluate the efficacy and applicability of the LM. The study will enrol 440 classes (around 8800 students, teachers and other personnel). Statistical units are represented by classes, randomized to LM or SoC.

The study will be carried out for 6 months, from October 2022 to March 2023 and includes two saliva tests a week. We assume that in the course of the investigated period the incidence rate of SARS-CoV-2 infection will change and this will allow us to test our hypotheses under different epidemiological conditions.

The randomisation will be applied as cluster randomisation: classes will be randomised in each school to the adoption of the LM or to SoC with contact tracing activity by public health departments and regular surveillance based on symptoms indicating testing. The two groups of classes will be compared in order to assess whether the LM will reduce the frequencies of attack rates/clusters dimension compared with classes on SoC. Logistics and costs affordability will also be evaluated.

An observational retrospective and prospective study will be carried out to investigate the prevalence of SARS-CoV-2 in schools with different variants, frequencies and size of clusters and attack rates in schools, the effect of different NPIs on SARS-CoV-2 diffusion in the schools and the related psychological effects. The study will involve classes/schools that are not involved in the interventional randomised study.

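### The 4% planning rate is described as an infection rate among contacts but used as the proportion of classes with a cluster, so the stated 80% power is not established for the weekly class endpoint

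*Protocol article*

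**What the plan says.** Under Determination of sample size, the only planning rate is introduced with "Given the average infection rates in contacts of about 4% per class [31"]. The same sentence concludes that "a sample size of 440 classes (220 per arm) achieves 80% power to detect a difference between the group proportions of 3.5" percentage points. The two hypotheses follow: "The proportion in arm with LM is assumed to be 4% under the null hypothesis and 0.05% under the alternative hypothesis". The test is named too: "The test statistic used is the one-sided Z test with pooled variance with a 5% significance level".

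Under Hypothesis, a cluster is two or more cases in one class within one school week, and "The main endpoint is the frequency of cluster per class in a scholar week". The Primary analysis section likewise compares clusters per class per week between arms. General study design makes the class the statistical unit, sets a duration of six months, and gives the size of the trial: "The study will enrol 440 classes (around 8800 students, teachers and other personnel").

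**The concern.** An infection rate in contacts is a risk per exposed person, and it presupposes that a case is already present. The proportion of classes with a cluster has classes as its denominator and also depends on how often a case enters a class. The endpoint adds a third element, the school week. The article moves from the first quantity to the second with no conversion and never reaches the third.

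At stake is the meaning of the 80% power and the 3.5-point difference. If the input is a rate of a different kind, neither figure shows what the 440 classes can detect on the main endpoint, and a negative result could not be set against them.

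**Working it through.** **Inputs from the article.** 220 classes per arm; 4% under the null; a difference of 3.5 points, which implies 0.5% under the alternative; 0.05% as printed; one-sided 5% Z test with pooled variance; 8800/440 = 20 persons per class, hence 19 contacts of one index case.

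**Step 1: reproduce the stated power.** Power = Φ[(d − 1.645·SE0)/SE1], where SE0 = √(2·p̄(1 − p̄)/n) and SE1 = √((p1(1 − p1) + p2(1 − p2))/n).
- 4% versus 0.5%, n = 220: d = 0.035, p̄ = 0.0225, SE0 = 0.01414, SE1 = 0.01404. Then (0.035 − 1.645 × 0.01414)/0.01404 = 0.836, and power is 79.8%. The size needed for 80% is 221 per arm.
- 4% versus the printed 0.05%, n = 220: power 90.5%, and 157 per arm would suffice.

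The stated 220 per arm and 80% therefore correspond to 4% versus 0.5% of classes, with one binary result per class. The 4% entered as a class proportion.

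**Step 2: what a 4% contact risk implies for a class.** Assume 19 equally exposed, independent contacts. Then P(at least one secondary case, given an index case) = 1 − 0.96^19 = 0.540. With 15 contacts it is 0.458, and with 24 it is 0.625. This holds only for a class that already has an index case. Writing q for the probability that a class has an index case in a given week, the class-week cluster rate is roughly 0.54·q. The article gives no q. The rate equals 4% only if q = 0.04/0.540 = 7.4%.

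This link is approximate. A secondary case may fall in the following week, and two unrelated cases in one week also meet the definition under Hypothesis.

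**Step 3: power of the stated test over a range of q.** Keep 220 per arm, one result per class, and the planned ratio 0.5/4 = 0.125.

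| q (assumed) | Control rate | LM rate | Power |
|---|---|---|---|
| 1% | 0.54% | 0.07% | 23% |
| 2% | 1.08% | 0.13% | 36% |
| 5% | 2.70% | 0.34% | 65% |
| 10% | 5.40% | 0.67% | 89% |
| 20% | 10.79% | 1.35% | 99% |

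**Step 4: effect of counting repeated weeks.** Suppose instead that 4% is already a weekly class rate. Assume 24 school weeks and a within-class correlation ρ. Effective class-weeks per arm = 220 × 24/(1 + 23ρ).

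| ρ (assumed) | Effective class-weeks per arm | Alternative detectable with 80% power |
|---|---|---|
| 0.02 | 5280/1.46 = 3616 | 2.9% |
| 0.05 | 5280/2.15 = 2456 | 2.7% |
| 0.10 | 5280/3.30 = 1600 | 2.4% |

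On this reading the trial could detect a much smaller effect than the planned fall to 0.5%. Steps 3 and 4 move in opposite directions, and the article does not say which situation applies.

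**The case against.** The best defence is that the sentence is only badly worded. The rate is given per class, it follows directly on a definition of clusters, and it feeds a proportion in a trial arm, so it may be a class-level figure after all. The cited source is not at hand to settle this. That doubt stands as far as the source is concerned. It does not rescue the calculation, because a class-level 4% with no time unit still cannot be matched to a weekly endpoint.

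A second defence is that the test has the right form: classes are the units, and the primary analysis compares frequencies between arms by Chi-square or Fisher test. That is fair. The arithmetic is sound once 0.5% is used; the fault lies in what the 4% measures.

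A third is that a correlation coefficient is commonly left to a fuller document. That is also fair, and its absence alone would be no finding. It enters here only because power for the endpoint cannot be restated without it.

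A reader might go further and infer that more than half of classes will have a cluster, and that power for a 3.5-point difference then falls to 18%. The documents do not support this. The 54% applies only where an index case is present. The 62% obtained as 1 − 0.96^24 is a cumulative risk that already takes 4% as a weekly class rate. The 18% (54% versus 50.5%) arises only from holding 3.5 points fixed at a quite different base rate. If the planned weekly rates are carried through 24 weeks, 62.5% versus 11.3% (1 − 0.995^24) of classes have a cluster, and power is close to 100%.

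**Conclusion.** The concern holds as a mismatch of input and endpoint. A per-person rate given a case is used as a class proportion, without conversion or time base, while the endpoint is counted per class and week. The stated 80% power belongs to 4% versus 0.5% of classes with one result each, and it is not established for the main endpoint.

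The documents do not show that the trial is underpowered, or overpowered. On one result per class, power runs from about 23% to 99% as q goes from 1% to 20%; on repeated weeks at 4%, the trial detects alternatives of about 2.4% to 2.9%. These ranges rest on assumed values of q, on 19 independent contacts, on 24 school weeks and on correlations of 0.02 to 0.10. None of these is stated in the article except the average class size behind the 19. The conflict between the printed 0.05% and the 3.5-point difference is visible on the page and needs no assumption.

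**What to change.** In Determination of sample size:

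- Replace the 4% with an assumed control-arm frequency of clusters per class-week, under the definition given in Hypothesis. Take it from standard-of-care or earlier school surveillance data, or show a range if no such figure exists. The LM pilots described in the article report positive cases and positivity rates under LM, so as reported they do not supply this control rate.
- State the number of school weeks and a within-class correlation, both as assumptions.
- Correct the alternative so that it agrees with the stated difference.
- Restate the power, or the detectable difference, that the fixed 440 classes give for the class-week comparison.

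The cost is a recalculation and a revised paragraph. No classes are added. The stated power may move in either direction, and the sponsor should be ready to report a figure other than 80%.

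### The printed 0.05% rate contradicts the 3.5% difference and the 80% power in the sample-size statement, and that power is for a one-sided Z test whose sidedness the primary analysis does not carry over

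*Protocol article*

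**What the plan says.** Under Determination of sample size, the protocol article states that "a sample size of 440 classes (220 per arm") "achieves 80% power to detect a difference between the group proportions of 3.5" per cent. The next sentence gives the rates: "The proportion in arm with LM is assumed to be 4% under the null hypothesis and 0.05% under the alternative hypothesis". The section closes with the test: "The test statistic used is the one-sided Z test with pooled variance with a 5% significance level".

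Under Primary analysis (LM evaluation trial), absolute and relative cluster frequencies by arm are to be "compared at univariate analysis with Chi Square or Fisher exact test, as appropriate". No sidedness is given there, nor any threshold for choosing between the two tests.

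The Hypothesis section is directional ("The main hypothesis is that the LM can reduce the frequency of clusters") and sets the unit of the endpoint: "The main endpoint is the frequency of cluster per class in a scholar week".

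**The concern.** There are two separate problems.

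First, the stated difference and the stated rates cannot both be right. They imply different effects: 4% to 0.5% is a relative reduction of 3.5/4 = 87.5%, and 4% to 0.05% is 3.95/4 = 98.75%. One of the figures on which the trial was sized is wrong as printed.

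Second, the power belongs to a one-sided Z test, whereas the analysis section names tests that are ordinarily run two-sided and, in Fisher's case, are also more conservative. If the ordinary two-sided forms are used, the advertised 80% does not describe the primary comparison. A null result would then be read against more power than the trial had.

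**Working it through.** **Inputs.** From Determination of sample size: n = 220 per arm, 1:1; p1 = 4%; p2 = 0.05% as printed, or 0.5% as implied by 4% − 3.5%; one-sided pooled Z test at 5%. From Primary analysis: chi-square or Fisher. The calculation treats each class as contributing one yes/no result, as the plan's own calculation does.

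**Difference.** 4% − 0.05% = 3.95 points; 4% − 0.5% = 3.5 points.

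**Formula (pooled variance).** With p̄ = (p1 + p2)/2,

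power = Φ{ [ |p1 − p2|·√n − z·√(2p̄(1 − p̄)) ] / √(p1(1 − p1) + p2(1 − p2)) }

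n per arm for 80% = { [ z·√(2p̄(1 − p̄)) + 0.8416·√(p1(1 − p1) + p2(1 − p2)) ] / |p1 − p2| }²

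Here z = 1.645 one-sided or 1.960 two-sided.

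**Step 1: reproduce the plan, 4% vs 0.5%, one-sided.**
- p̄ = 0.0225; 1.645 × √(2 × 0.0225 × 0.9775) = 0.3450
- √(0.0384 + 0.004975) = 0.2083; 0.035 × √220 = 0.5191
- Power = Φ[(0.5191 − 0.3450)/0.2083] = Φ(0.836) = 79.8%
- n = [(0.3450 + 0.8416 × 0.2083)/0.035]² = 220.96, so 221 per arm

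This matches the stated 80% and 220 per arm.

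**Step 2: the printed rate, 4% vs 0.05%, one-sided.**
- p̄ = 0.02025; 1.645 × √(2 × 0.02025 × 0.97975) = 0.3277
- √(0.0384 + 0.00049975) = 0.1972; 0.0395 × √220 = 0.5859
- Power = Φ[(0.5859 − 0.3277)/0.1972] = Φ(1.309) = 90.5%
- n = [(0.3277 + 0.8416 × 0.1972)/0.0395]² = 156.2, so 157 per arm (314 classes)

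This does not match. Two-sided at 0.05% gives 83.9% and 199 per arm, which does not match either. Two-sided at 0.5% gives Φ[(0.5191 − 0.4111)/0.2083] = Φ(0.519) = 69.8% and 281 per arm, again no match. Of the four combinations, only 0.5% with a one-sided test returns the plan's figures.

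**Step 3: power of the named tests at 4% vs 0.5%, 220 per arm.** The exact column sums the binomial probabilities of all outcomes that the test rejects. The rule uses Fisher when the expected cluster count per arm, computed from the observed total, is below 5, and chi-square otherwise. That threshold is an assumption, since the protocol gives none.

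| Test at 5% | Planning formula | Exact enumeration |
|---|---|---|
| One-sided pooled Z (chi-square read one-sided) | 79.8% | 85.4% |
| Two-sided chi-square, uncorrected | 69.8% | 74.8% |
| Two-sided Fisher | – | 62.5% |
| Two-sided chi-square-or-Fisher rule | – | 66.9% |
| One-sided Fisher | – | 73.6% |
| One-sided chi-square-or-Fisher rule | – | 77.6% |

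**Step 4: how often Fisher would be chosen.** Expected clusters are 220 × 4% = 8.8 and 220 × 0.5% = 1.1, so the average per arm is (8.8 + 1.1)/2 = 4.95, just under 5. Under the rule above, Fisher is selected in about 47% of outcomes.

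**The case against.** The best defence has four parts.

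1. The 0.05% changes nothing in the design. The 3.5% difference, the 220 per arm and the 80% all agree with 0.5%, so only one printed number is out. This stands. A reader might infer that the sample size was miscalculated, but Step 1 shows that it was not.

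2. The uncorrected chi-square statistic is the square of the pooled Z, so on that branch the two sections name the same statistic. Only sidedness can differ, and the analysis section gives none. The Hypothesis section is directional and the sample-size section says one-sided 5%, so a one-sided reading that keeps about 80% is available. This also stands. A reader might infer that the trial does not deliver its stated power. The document does not establish that, because the shortfall arises only if the tests are run two-sided or if Fisher is used. If 0.05% were really meant, two-sided power would exceed 80% anyway: 83.9% for chi-square by formula and about 85% for Fisher by enumeration.

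3. The expected count of 4.95 might suggest that Fisher will be the test used. It does not: the rule picks Fisher in slightly under half of outcomes, and the protocol sets no threshold.

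4. A prespecified one-sided test of a directional hypothesis is a design choice and not an error. It cannot show an excess of clusters under LM, which the more intensive testing in that arm could produce. That is a reason to consider a two-sided test, but nothing in the document makes one obligatory.

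The defence does not remove the arithmetic contradiction, nor the fact that two sections describe the primary test differently. Nor does it rescue the Fisher branch, which falls below 80% at 0.5% whichever sidedness is chosen.

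**Conclusion.** The sample-size statement is wrong as written. A 3.5-point difference, 80% power and 220 per arm agree with 0.5% and not with the printed 0.05%, which would mean 90.5% power or 157 per arm. A decimal slip is very probable, but only the sponsor can confirm it.

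The test mismatch is real, with a conditional consequence. Taking 0.5% as intended and the tests in their ordinary two-sided form, exact power with 220 per arm is 74.8% for chi-square, 62.5% for Fisher and about 67% for the rule. On the planning formula, chi-square has 69.8% against the stated 80%. With a one-sided analysis, chi-square keeps about 80%, Fisher has 73.6% and the rule about 78%.

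All these figures take one binary result per class, as the plan's calculation does. The endpoint is defined per class and school week, so they test the consistency of the stated calculation and do not forecast power on class-weeks.

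**What to change.** - In Determination of sample size, make the LM rate agree with the 3.5% difference, after the sponsor confirms which figure was intended. The stated size and power point to 0.5%.
- Name one primary test and one sidedness, in the same words, in Determination of sample size and in Primary analysis (LM evaluation trial). Either write one-sided 5% explicitly into the analysis section, with about 80% power for the pooled Z/chi-square test, or adopt two-sided 5% and state the lower power.
- Restate the power of 440 classes for the chosen test using a single calculation method. The planning formula and exact enumeration differ by about 5 points here (79.8% and 85.4% one-sided; 69.8% and 74.8% two-sided chi-square), so figures from the two should not be mixed.

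The cost is protocol text only, with no change in enrolment. The drawback is that the stated power may become less favourable.
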